##### HYPOTHESIS

Personalised, risk-based screening for and early treatment of adverse events in HL survivors, according to the BETER guidelines, leads to reduced burden of disease from late effects, lower healthcare costs, better quality of life and reduced productivity loss compared to the absence of structured survivorship care.

##### RESEARCH QUESTION

Compared to usual care (absence of structured survivorship care), is survivorship care at the BETER clinics effective in 1) reducing morbidity and mortality from late effects of lymphoma treatment and associated costs; 2) increasing health-related quality of life and 3) reducing productivity losses?

What are the adherence rates to the BETER guidelines from patient and health care provider perspectives and what specific (parts of the) guidelines have lower adherence?

Which patient characteristics are associated with lower attendance rates to the BETER clinic?

Is knowledge about late adverse effects, risk perception of and distress about late effects associated with BETER clinic attendance and adherence to the screening guidelines?

## Plan van Aanpak / Strategy

### 1. DESCRIPTION OF CLINICAL STUDY

#### 1.1. DESIGN

The proposed study is a retrospective cohort study with a quasi-experimental design. The intervention group consists of Hodgkin lymphoma (HL) survivors who were invited to first visit a BETER clinic in 2013-2016 and the control group consists of survivors eligible for BETER survivorship care as of 2013-2016, but treated in hospitals starting a BETER clinic later, in 2021-2024. In this design we make use of the gradual introduction of BETER survivorship care in the Netherlands, as not all centres participating in the BETER consortium were able to provide BETER care immediately. This was because it took time to identify and trace the eligible patient population and set up the local infrastructure, such as for referral to cardio-oncology and other specialist care.

For the conduct of the study, we also have the unique opportunity to use a previously established comprehensive data set from a large nationwide retrospective cohort of all lymphoma survivors treated in 27 BETER centres between 1965-2012, with patient characteristics, treatment data, and outcome data (such as dates of diagnosis of second cancers, cardiovascular events, date and cause of death). This allows selection of a control population of individuals who were not yet screened during 2013-2016, frequency matched to the intervention group on age and year of lymphoma diagnosis, and lymphoma treatment. Additional follow-up data for all included survivors will be collected through disease registries and survivors' general practitioners without burdening the study population. The comprehensive dataset enables comparison of the intervention and control group and assessment of characteristics of non-responders to BETER survivorship care.

1.1.1. Considerations about other study designs: The ideal design to evaluate the (cost-)effectiveness of BETER survivorship care would have been a randomized controlled trial (RCT), randomizing patients to receive either BETER care or no BETER care (which generally would imply no survivorship care at all). Such a design is not possible because it was deemed to be unethical to withhold BETER care from eligible survivors when BETER care was introduced, as their risks of late adverse effects are high and the benefits of screening for breast cancer and cardiovascular disease (CVD) have been demonstrated in other high-risk groups (9,10) and implied by single screening modality studies in lymphoma survivors (11,12). Moreover, when the screening recommendations developed by the BETER consortium were approved by the respective scientific national medical societies, health care professionals were bound to adhere to them.

Alternatively, an effectiveness study with a stepped wedge design was considered, randomizing centres between immediate introduction of BETER care or waiting several years, while BETER care was gradually introduced. However, again on ethical and regulatory grounds, this was not feasible because centres did not want to postpone initiation of BETER survivorship care when they were ready to start. A pre-test post-test control group design, also called the classic controlled experimental design, was not possible either, as baseline measurement in both patients in BETER participating centres and centres not yet participating could not be performed: most survivors eligible for BETER were discharged many years ago and treating physicians considered it unethical to invite them back to the hospital for a baseline assessment only, without subsequently offering them survivorship care according to the BETER guidelines.

In summary, an RCT, a stepped wedge design and a pre-test post-test control group design evaluating BETER survivorship care versus absence of structured survivorship care were not feasible due to ethical and regulatory objections.

#### 1.2. PATIENT (P)

##### 1.2.1. Patient population

The study will be nested in a large nationwide retrospective cohort study of HL survivors treated in 27 Dutch centres between 1965 and 2012 (15,16). This cohort was originally established in the 1980s-1990s to examine the late effects of HL treatment; since then the cohort has been periodically extended with more treatment centres, patients diagnosed in more recent years and with diffuse large B-cell lymphoma (DLBCL) survivors diagnosed between 1989 and 2012. Lymphoma survivors eligible for BETER survivorship care were successfully treated at least 5 years ago for HL or DLBCL at age 15-60 years and are less than 70 years of age at invitation. The patient population in this evaluation study will only consist of HL survivors eligible for BETER survivorship care, as they were the first to be invited to the BETER clinics in 2013-2016 due to their higher risk of late adverse treatment effects compared to DLBCL survivors.

1.2.2. Intervention group: the first 450 HL survivors between 2013 and 2016 who were invited for screening for late adverse treatment effects in the BETER centre where they were originally treated for HL. With attendance rates ranging between 60-70%, around 300 HL survivors in the intervention group are expected to receive screening at the BETER clinics.

1.2.3. Control group: frequency matched group of 450 HL survivors, eligible for BETER screening for late adverse treatment effects in 2013-2016, but not yet invited because the centre where they were originally treated for HL does not start a BETER clinic until 2021-2024. So, the control group will be invited in 2021-2024.

Controls will be matched with the intervention population on the following criteria:

- sex
- age at diagnosis ( $\pm 3$  years)
- year of diagnosis ( $\pm 3$  years)
- lymphoma treatment characteristics associated with increased risk of CVD, breast cancer, hypothyroidism and functional asplenia (see also 1.3.1.). In practice this implies matching on chest radiotherapy (y/n), neck radiotherapy (y/n), spleen radiotherapy (y/n), splenectomy (y/n) and anthracyclines (y/n + doxorubicin  $\approx 300$  mg/m^2 y/n).

Survivors selected as controls should be alive at the time the corresponding survivor in the intervention group was invited to

come to the BETER clinic. Of note, matched controls eligible for BETER screening in 2013-2016 who died during follow-up, prior to invitation for BETER screening in a BETER clinic 2021-2024, are eligible for our study.

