### 1.8. DATA-ANALYSIS

#### 1.8.1. Intention to screen analysis

To assess the impact of BETER survivorship care on the centres' eligible lymphoma population, the outcome parameters will be compared between the first 450 survivors who were invited to a BETER clinic that started in 2013-2014 and 450 matched survivors who were treated for lymphoma at BETER centres that does not start a clinic until 2021-2024. Reasons why participating centres did not start a BETER clinic before 2021 are of logistic nature involving identification and tracing of patients and setting up the infrastructure, especially the availability of an interested cardiologist and a nurse-practitioner; factors very unlikely to be associated with treatment-specific risks of late effects and our study outcomes. Centres starting an early BETER clinic included both University Medical Centres and large peripheral hospitals. This allows us to use an instrumental variable analysis with the variable 'treated for lymphoma at a centre with a BETER clinic that started in 2013-2014' (y/n) as instrumental variable. We hereby mimic randomization and minimize the risk of bias in this observational study. The variable 'treated for lymphoma at a centre with a BETER clinic that started in 2013-2014' is strongly associated with the likelihood of

receiving the intervention (65% vs. 0-5% for clinics that started in 2013-2014 and 2021-2024 respectively), but not associated with any prognostic factor or with the outcome (other than through the intervention). The attendance rates are based on preliminary data from a small study in a few BETER clinics which showed that the attendance rate was 60-70% and that survivors only rarely visited a BETER centre not connected to their original lymphoma treatment centre. Individual matching of control group participants to the intervention group on relevant treatment characteristics will control for any differences in lymphoma treatment between centres.

When we select the matched comparison group eligible for BETER care in 2013-2016, we do not yet know whether they will attend the BETER clinic when invited in 2021-2024; therefore, in a truly unbiased analysis, attendance should not be an eligibility criterion in the intervention group as well. Our intention-to-screen analysis is therefore the most valid approach to evaluation of the cost-effectiveness of BETER survivorship care.

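### The intervention arm is restricted to survivors who were invited, but controls need only be eligible and alive, so the intention-to-screen analysis does not compare the centres' eligible populations

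*Protocol*

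**What the plan says.** The two arms are entered by different rules.

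- **Intervention arm (1.2.2):** "the first 450 HL survivors between 2013 and 2016 who were invited for screening", at the centre where they were treated.
- **Control arm (1.2.3):** survivors "eligible for BETER screening for late adverse treatment effects in 2013-2016, but not yet invited because the centre where they were originally treated" had no clinic until 2021-2024. The condition on vital status is: "Survivors selected as controls should be alive at the time the corresponding survivor in the intervention group was invited". Matched controls "who died during follow-up, prior to invitation for BETER screening in a BETER clinic 2021-2024, are eligible for our study".
- **Eligibility (1.2.1):** successful treatment at least 5 years earlier, age 15-60 at treatment, and survivors must be such that they "are less than 70 years of age at invitation". Nothing concerns current health or whether the person can be found.
- **Matching (1.2.3):** sex, age and year of diagnosis, and lymphoma treatment.
- **Consent (1.6.1.1):** taken at the clinic visit, or requested by mail from those who choose not to attend. Deceased controls need none.
- **Analysis (1.8.1):** the stated aim is the effect on the eligible lymphoma population of the centres. The instrument is being "treated for lymphoma at a centre with a BETER clinic that started in 2013-2014". The section argues that attendance must not be an entry condition for the intervention arm, because it is unknown for controls at selection.
- **Tracing (1.1):** not all centres could offer BETER care at once, partly because "it took time to identify and trace the eligible patient population".

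**The concern.** With treating centre as the instrument, the group to set against late-centre survivors is every eligible, living survivor of the early centres. Section 1.2.2 keeps only those who received an invitation. Invitation comes after the instrument and is imposed in one arm only, so the argument that centre is unrelated to prognosis does not carry over to the people actually compared.

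The protocol's reasoning about attendance applies equally to invitation: for controls it is unknown who could have been traced and invited in 2013-2016. One asymmetric filter has been removed and the one before it left in place. Matching does not address health or traceability at the start of follow-up.

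At stake is the primary DALY outcome in the analysis that 1.8.1 regards as its most valid, and the cost-effectiveness model that draws on it. Section 1.6.1.2 charges each death with the full standard life expectancy at that age, so a few deaths can move the mean.

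**Working it through.** **1. The plan's own figures.** From 1.7.1: 1.18 DALYs over 5 years unscreened, 0.56 screened, attendance 65%, average age 52.
- Intervention mean: 0.65 × 0.56 + 0.35 × 1.18 = 0.777, stated as 0.78.
- Difference: 1.18 − 0.777 = 0.403, stated as 0.40.
- From 1.7.2, two-sided 0.05, 80% power, 0.20 SD: n = 2 × (1.960 + 0.842)² / 0.20² ≈ 393 per arm, as stated.

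**2. Who enters.** Take two eligible, living survivors who are alike, one from each type of centre, neither of whom could have been traced in 2013-2016.

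| | Early centre | Late centre |
|---|---|---|
| Alive in 2021-2024 | in neither arm | control, if reached for consent |
| Died during follow-up | in neither arm | control, no consent needed |

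Section 8.5.1 secures date and cause of death for those invited, whether or not they attended. It is silent on early-centre survivors who were never invited.

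**3. Form of the bias.** With no true benefit, the expected difference between arms is

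bias = (share of eligible survivors not invited) × (their excess DALYs over the invited).

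The protocol gives neither term, so these are assumptions:
- 5% × 2 DALYs = 0.10
- 10% × 2 DALYs = 0.20
- 10% × 4 DALYs = 0.40, the whole expected effect

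**4. Tipping point in deaths.** Excess risk of target-cause death needed = 0.40 / (years of life lost per death). The years per death are assumed.

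| Years lost per death | Excess risk | Deaths per 450 |
|---|---|---|
| 20 | 2.00% | 9.0 |
| 25 | 1.60% | 7.2 |
| 30 | 1.33% | 6.0 |
| 35 | 1.14% | 5.1 |

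Only deaths from cardiovascular disease, breast cancer, hypothyroidism or functional asplenia count (1.6.1, 1.6.1.2).

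**5. Consequence for the test.** No SD is stated. If 0.40 DALY is taken as 0.20 SD, then SD = 0.40 / 0.20 = 2.0. With 393 per arm, the standard error is 2.0 × √(2/393) = 0.143. With no true effect, the chance of a significant result favouring BETER is Φ(bias / 0.143 − 1.96): about 10% at a bias of 0.10, 29% at 0.20 and 80% at 0.40.

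**The case against.** A reader might infer that survivors too ill to invite were left out of the intervention arm and that their deaths in the control arm will be counted as benefit. The protocol does not support this.

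- No section says that ill survivors were withheld from invitation or that a physician chose whom to approach. Section 1.6.2.2 points somewhat the other way: prior diagnosis of adverse events elsewhere was a common reason for not attending, so such people had been invited and stay in the intervention arm.
- Tracing is given in 1.1 and 1.8.1 as a reason why centres started late. Neither section says that early centres failed to trace anyone, or how many.
- The first 450 may simply be a cap on a continuing roll-out, so that others were invited later.
- Living controls must also be reached for consent. The sharp asymmetry concerns deceased controls.
- Untraced survivors could be healthy people discharged long ago, which would bias against BETER.
- The tipping point is solved backwards. An excess of 0.40 is 0.40 / 1.18 = 34% of the whole modelled control burden. At 30 years per death, 1.18 DALYs is at most 1.18 / 30 × 450 = 17.7 deaths, so 6 excess deaths is a worst case and not an expected bias.

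All of this stands as a limit on direction and size. None of it removes the difference in entry rules, which no section repairs.

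**Conclusion.** The concern holds as a defect of design and wording. The intervention arm is conditional on invitation and the control arm is not, so 1.8.1 does not compare the centres' eligible populations as it claims, and the centre instrument does not correspond to the invited-only arm. Bias in favour of BETER care is plausible, because a control who could not be traced is most surely retained if deceased, but it is not demonstrated.

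The size is unknown. The 5 to 9 excess target-cause deaths per 450 controls rest on an assumed 20 to 35 years of life lost per death and show only how few deaths would suffice. The false-positive figures rest further on an inferred SD of 2.0. Neither set should be read as an estimate of the bias.

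**What to change.** 1. Keep the invited sample of 1.2.2 for outcomes that need consent or contact.
2. Add to 1.8.1 a by-centre analysis of mortality and years of life lost from the existing cohort file. Define both arms by one rule: eligible, under 70, at least 5 years after treatment and alive at an index date assigned in the same way in both arms, grouped by early or late treating centre, whether or not invited. Use the date and cause of death that 1.1 and 8.5.1 say the cohort holds.
3. Report the numbers eligible, traced and invited for each early centre.
4. Limit the claim in 1.8.1 that the design imitates randomisation, so that it does not cover the invited-only comparison.

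**Cost.** Redrawing the whole intervention arm would be more than a new query, since 1.6.1.1 has no consent route for survivors who were never invited. The added analysis avoids most of that, but the protocol does not state whether the cohort's death data already run to 2021-2024, so an update may be needed.

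Uptake in the early-centre arm falls, and with it the expected difference. If 90% of eligible survivors were invited (assumed), uptake is 0.90 × 0.65 = 58.5% and the expected DALY difference 0.585 × 0.62 = 0.36; at 80% invited it is 0.52 × 0.62 = 0.32. The symmetric comparison covers years of life lost only. Years lived with disability, costs and QALYs still rest on the invited sample.

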#### 1.3.1. BETER Screening Recommendations for Late Adverse Effects after Lymphoma Treatment

##### 1.3.1.1. Cardiovascular Disease

RISK: standardized incidence ratio (SIR) of 2-6 and a 40-year cumulative incidence of 50% (at age 65) (16).

SUBGROUP OF LYMPHOMA SURVIVORS: treated with cardiotoxic chemotherapy (doxorubicin, epirubicin, rubidomycin, daunorubicin, mitoxantrone) with cumulative doses equivalent to doxorubicin =300 mg/m^2, radiotherapy to the mediastinum or radiotherapy to the mediastinum in combination with cardiotoxic chemotherapy, independent of cumulative dose.

SCREENING: screening of cardiovascular risk factors every 5 years, up to age 70 (medical history, physical examination and blood tests: lipid spectrum, glucose, biomarkers BNP or NTproBNP as a reference for follow-up), screening for valvular disease and subclinical heart failure by cardiac ultrasound only once 15 years after diagnosis in case of radiotherapy mediastinum and every 5 years in case of cardiotoxic chemotherapy (with/without mediastinal radiotherapy) and ECG (once as a reference).

TREATMENT AND/OR PREVENTION OF LATE ADVERSE EFFECTS: treatment of cardiovascular risk factors hypertension and hypercholesterolemia, treatment in case of subclinical decrease of ejection fraction and lifestyle recommendations in accordance with general population guidelines.

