##### 1.3.1.2. Breast Cancer

RISK: SIR 4-6 and a 30-year cumulative incidence of 17-26% at age 55 (15).

SUBGROUP OF LYMPHOMA SURVIVORS: women treated with radiotherapy on chest and/or axillae before the age of 40 years.

SCREENING: age 25-30: annual clinical breast examination and magnetic resonance imaging (MRI); age 30-60: annual clinical breast examination, mammography and MRI; age 60-70: biennial clinical breast examination and mammography; age 70-75: biennial mammography through population screening.

TREATMENT AND/OR PREVENTION OF LATE ADVERSE EFFECTS: take previous chest radiation treatment into account and consider risk of cardiomyopathy when using anthracyclines.

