##### 1.3.1.4 Overwhelming Post-Splenectomy Infections

RISK: relative risk up to 20 (17).

SUBGROUP OF LYMPHOMA SURVIVORS: treated with splenectomy, splenic radiotherapy (mean dose >20 Gy) or stem cell transplant.

SCREENING: none.

TREATMENT AND/OR PREVENTION OF LATE ADVERSE EFFECTS: vaccinations for Pneumococcus (start with Prevenar-13, followed by Pneumovax-23 two months later; Pneumovax-23 every 5 years), Haemophilus Influenzae B once, Meningococcus once, Influenza annual; medical alert card, travel advice and antibiotics on demand.

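### The matching list in section 1.2.3 does not fully reproduce the section 1.3.1 risk groups it refers to, so section 1.8.1 claims too much for it

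*Protocol*

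**What the plan says.** Section 1.2.3 introduces the matching with "Controls will be matched with the intervention population on the following criteria". It lists sex, age at diagnosis and year of diagnosis (each within 3 years), and "lymphoma treatment characteristics associated with increased risk of CVD, breast cancer, hypothyroidism and functional asplenia (see also 1.3.1". It then gives the working version of that last item: "matching on chest radiotherapy (y/n), neck radiotherapy (y/n), spleen radiotherapy (y/n), splenectomy (y/n) and anthracyclines (y/n", with a further yes/no indicator for doxorubicin at 300 mg/m² inside the anthracycline item ("splenectomy (y/n) and anthracyclines (y/n + doxorubicin").

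Section 1.3.1 defines the groups at risk:

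- Asplenia (1.3.1.4): "treated with splenectomy, splenic radiotherapy (mean dose >20 Gy) or stem cell transplant".
- Cardiovascular disease (1.3.1.1): mediastinal radiotherapy alone, mediastinal radiotherapy with cardiotoxic drugs at any dose, or "cardiotoxic chemotherapy (doxorubicin, epirubicin, rubidomycin, daunorubicin, mitoxantrone) with cumulative doses equivalent to doxorubicin" 300 mg/m².
- Breast cancer (1.3.1.2): "women treated with radiotherapy on chest and/or axillae before the age of 40 years".
- Thyroid dysfunction (1.3.1.3): radiotherapy to the thyroid region.

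Section 1.8.1 concludes: "Individual matching of control group participants to the intervention group on relevant treatment characteristics will control for any differences in lymphoma treatment between centres". Sections 1.1 and 1.2.3 call the matching frequency matching; 1.8.1 calls it individual.

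**The concern.** The comparison is not randomised and has no baseline measurement (1.1.1). Quality of life and productivity are measured once, at the end of follow-up, and the reply in 8.3.1 rests the validity of those comparisons on the matching. Lymphoma treatment determines the risk of the outcomes and also, under 1.3, what BETER care consists of for a given survivor. If the matching list leaves out treatment factors that the protocol itself treats as defining risk, two survivors, or two arms, can agree on every listed factor and still differ in 1.3.1 risk group. Any such difference between early and late centres would be read as an effect of BETER care. It would also count against the premise in 1.8.1 that the centre's start date is unrelated to prognosis. The matching is fixed in the protocol and carried out when controls are drawn, so it is hard to repair later.

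**Working it through.** **Step 1. The two lists side by side.**

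| Criterion in 1.3.1 | Matching in 1.2.3 | Result |
|---|---|---|
| Splenectomy | yes/no | reproduced |
| Splenic radiotherapy, mean dose >20 Gy | spleen radiotherapy yes/no | dose criterion lost |
| Stem cell transplant | none | absent |
| Cardiotoxic drug exposure, five agents | anthracyclines yes/no | covered as exposure; treatment of mitoxantrone not stated |
| Doxorubicin-equivalent dose, 300 mg/m² | indicator names doxorubicin only | reproduced for doxorubicin; not stated for the other agents |
| Mediastinal radiotherapy | chest yes/no | probably a close proxy; coding not defined |
| Thyroid-region radiotherapy | neck yes/no | probably a close proxy; coding not defined |
| Chest and/or axillary radiotherapy | chest yes/no | axillary field not named |
| Female, irradiated before 40 | sex, and age at diagnosis within 3 years | reproduced except near age 40 |

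One criterion is missing outright (transplant). Three are matched more coarsely than they are defined: spleen dose, equivalent dose and axillary field. The age limit is matched approximately. The rest is reproduced or plausibly proxied.

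**Step 2. Where the gaps fall in the planned outcome.** Inputs are from section 1.7.1.

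- Planned difference: 0.65 × 0.56 + 0.35 × 1.18 = 0.364 + 0.413 = 0.777, and 1.18 − 0.777 = 0.403. This reproduces the stated 0.40 DALY.
- Asplenia without screening: 0.04 / 1.18 = 3.4% of the burden. If the arms differed by the whole 0.04, the shift would be 0.04 / 0.40 = 10% of the planned difference.
- Breast cancer and cardiovascular disease: 1.12 / 1.18 = 95% of the burden. The equivalent-dose and axillary gaps bear on this part.

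The two clearest gaps (transplant and spleen dose) define the smallest component that could matter. Transplant might also mark heavier earlier treatment, but the protocol does not say so.

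**Step 3. How far the age limit matters.** Assume individual matching, ages uniform over a range of width R, and a control drawn uniformly within 3 years. A person d years from 40 (d < 3) is matched across 40 with probability (3 − d)/6. Summed over both sides this is 2 × (9/2)/6 = 1.5 person-years, so the crossing share is 1.5/R, ignoring the ends of the range. For ages 15–60 (R = 45) that is 3.3%; for a 30-year range it is 5.0%. It is relevant only for irradiated women, and crossings occur in both directions.

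**Step 4. Does the claim in 1.8.1 follow?** Matching can balance only what is matched or is closely tied to it. Since step 1 shows treatment criteria that are neither matched nor clearly proxied, control of any treatment difference does not follow from the list.

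**The case against.** The strongest case against is that the list is already good. It matches sex, age and year of diagnosis, anthracycline exposure, splenectomy, three radiotherapy fields and the 300 mg/m² doxorubicin indicator. Year of diagnosis also stands in for treatment era. The dose item may be shorthand for equivalent dose, since the bullet refers to 1.3.1. Under 1.3.1.1, mediastinal radiotherapy puts a survivor in the cardiovascular group whatever the dose, so the dose indicator decides membership only for those without it. Section 1.8.2 plans multiple regression; it names only follow-up time, but other covariates may be set in an analysis plan that is not shown. All of this stands and limits the point. It does not supply the missing transplant factor, settle how the other agents are coded, or support a claim about any difference.

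Three stronger readings are tempting.

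- *A numerical bias.* A reader might turn the gaps into a percentage of the 0.40 DALY. That needs the share of survivors in each risk group, their relative burden and the net imbalance between arms. The documents give none of these, and with no net imbalance the bias is zero.
- *A failure at age 40.* A reader might note that a woman of 38 can be matched to one of 41. Such crossings are symmetric and few (step 3). If chest radiotherapy included the mediastinum, both women are in the cardiovascular group. Controls receive no BETER care during follow-up, so a control's screening entitlement alone biases nothing.
- *Early and late centres treated differently.* Section 1.8.1 says early starters included both university and large peripheral hospitals. That does not show a difference from late starters.

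**Conclusion.** The point holds in a limited form. The practical matching list omits stem cell transplant and is coarser than 1.3.1 on spleen dose, doxorubicin-equivalent dose and axillary field, so imbalance on these factors is possible and the sentence in 1.8.1 is too absolute. The documents do not show that imbalance exists, and neither its size nor its direction can be derived from them. The one available bound is for asplenia: at most 0.04 DALY, or 10% of the planned difference, if the arms differed by that entire component. The conclusion assumes that the list in 1.2.3 is complete as written, and that chest and neck are adequate stand-ins for mediastinum and thyroid region. The conflict between frequency and individual matching affects how the issue is framed (balance of groups or of pairs) but does not remove it. This is an inexpensive improvement worth making before controls are selected; it does not invalidate the design.

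**What to change.** Reconcile 1.2.3 with 1.3.1 and 1.8.1 before controls are drawn:

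1. Add stem cell transplant (yes/no) to the matching factors.
2. Define the existing dose indicator as doxorubicin-equivalent cumulative dose over all agents listed in 1.3.1.1, including mitoxantrone.
3. Pre-specify the remaining 1.3.1 indicators as regression covariates and not as further matching strata: the spleen dose criterion, axillary field, and female sex with radiotherapy before the age limit in 1.3.1.2. Use an unknown category where the cohort does not record them. The age and year calipers then need not be widened.
4. Report balance on all these indicators by arm.
5. Restate 1.8.1 as controlling for the listed treatment characteristics.
6. State once, in 1.1, 1.2.3 and 1.8.1, whether matching is by frequency or individual.

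The cost is protocol wording, slightly fewer exact matches and a few more model terms. Section 1.1 says the cohort holds treatment data but not at what level of detail, so some indicators may be incompletely recorded.
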